### Secondary outcomes

2.9

The secondary outcome measures include weekly mean frequency of defecation, weekly mean stool appearance score, weekly mean stool urgency score, emotional state score, gut microbiome, and faecal metabolome.(1)Similarly, based on the diary (Appendix 2), the weekly mean frequency of defecation, the weekly mean stool appearance score, and the weekly mean stool urgency score within the past two weeks on day 0, day 14, day 28 to day 42 will be evaluated. It is noted that the weekly mean frequency of defecation, weekly mean stool appearance score, and the weekly mean stool urgency score on day 0 are obtained from the diary completed during screening period, Table 1.(2)The Depression, Anxiety and Stress Questionnaire (DASS-21) [38] (Appendix 3) will be completed online on day 0 (baseline), day 14, day 28, and day 42, and emotional state score calculated from DASS-21 will be used to assess the volunteers' emotional status, Table 1.(3)For the indicator of gut microbiome, DNA are extracted from stool sample using the QIAamp Fast DNA Stool Mini Kit (Qiagen, Hilden, Germany). An agarose gel electrophoresis and Nanodrop spectrophotometer are used to examine the quality of DNA. Then, shotgun metagenomic sequencing are performed for all samples using an Illumina HiSeq 2500 instrument. And sequence libraries are constructed by DNA fragments of ∼300 bp length which obtained from paired-end reads of ∼150 bp lengths generated by sequencing in bi-directions. In addition, the metagenomic analysis is performed from the following aspects: analysing alpha diversity and beta diversity in each group to determine the intra-groups differences in the microbiota compositions; analysing the inter- and intra-groups taxonomic characteristics at the levels of phylum, genus, and species to identify specific genes related to diarrhoea. Metagenomic biological pathway analysis are used to evaluate the effect of probiotics on the function of the gut metagenomics in patients with diarrhoea and hopefully to explore the metagenomic biological pathways contributing to the mechanism of probiotics on the treatment of diarrhoea.(4)For the indicator of faecal metabolome, briefly, stool samples treated by protein precipitation method and the supernatant are used for liquid chromatography tandem mass spectrometry (LC-MS/MS) analysis. The original data is subjected to peak alignment, retention time correction and peak area extraction through the XCMS-Plus program. The structure of metabolites is identified by accurate mass matching (<5 ppm) and two-level spectrum matching, and METLIN database is retrieved. After deleting the missing value > 50% and normalizing the data, multi-dimensional statistical analysis is performed, like unsupervised principal component analysis (PCA), supervised partial least squares discriminant analysis (PLS-DA) and potential difference metabolite analysis. Metabonomic analysis can further identify the potential differential metabolites of probiotics in treatment of diarrhoea and examine the correlation analysis between the gut microbiota and metabolites.

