**Method:**

A randomized, double-blind, placebo-controlled clinical trial is designed to pinpoint the efficiency and possible action modes of probiotics for chronic diarrhoea. 200 eligible volunteers with chronic diarrhoea are randomly assigned to a probiotic group (orally taking *Lactobacillus plantarum* p9 probiotics powder) or a placebo group. Except an independent project administrator who will be responsible for unblinding, the other researchers are blinded. Primary outcome is diarrhoea severity score, and secondary outcomes include weekly mean frequency of defecation, weekly mean stool appearance score, weekly mean stool urgency score, emotional state score, gut microbiome, and faecal metabolome. Each outcome measure will be assessed at the timepoints of pre-administration (day 0), administration (day 14 and/or 28), and post-administration (day 42) to identity inter- and intra-groups differences. Adverse events will be recorded to evaluate the safety of *L. plantarum* p9.

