	Gut microbiome		**✓**		**✓**	**✓**
	Faecal metabolome		**✓**		**✓**	**✓**
Safety measures	Adverse events (AEs)			**✓**	**✓**	**✓**
	Serious adverse events (SAEs)			**✓**	**✓**	**✓**
Verification of compliance with the intervention					**✓**	
Special situations related to defecation (e.g., concomitant medications)			**✓**	**✓**	**✓**	**✓**

Note: The outcome measures, weekly mean frequency of defecation, weekly mean stool appearance score and weekly mean stool urgency score are calculated from the defecation diary. The defecation diary completed from day −14 to −1 will be used for volunteer selection and baseline data. The detection of gut microbiome will be conducted within 2 months after the end of follow-ups, and the detection of faecal metabolome will be implemented within 2 months when data analysis finds that the probiotics present significant effect on gut microbiome.

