**Table 3 tbl3:** The format to analyse and present the intra-group differences among the four observation points in a probiotic or placebo group.

Groups	P5	P25	Median	P75	P95	H value	*P*
Day 0							
Day 14							
Day 28							
Day 42							

Note: The data here includes the diarrhoea severity score, weekly mean frequency of defecation, weekly mean stool appearance score, weekly mean stool urgency score, and emotional state score; P5, P25, P75, P95 means the 5th, 25th, 75th, 95th percentile, respectively; H is calculated using method of *Kruskal-Wallis* rank sum test.

In addition, the statistical analyses of metagenomics and metabolomics will be performed using the R software (v.4.0.2) and Adobe Illustrator. PCA and PLS-DA analysis will be performed and visualized using the R package vegan, ggplot and ggpubr, and the adonis *P*-value will be generated based on 999 permutations. *t*-test, *Wilcoxon* test and *Kruskal-Wallis* test will be used to evaluate differences in various variables between and within groups; *P* values will be corrected for multiple testing using the Benjamini-Hochberg procedure. Meanwhile, Pearson and spearman correlations will be used to analyse the correlations between different indicators in clinical, metagenomics and metabolomics.

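### Section 2.9 plans alpha and beta diversity as within-group analyses, at odds with the between-group aims stated elsewhere, and the metabolome gate does not say which microbiome comparison counts

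*Protocol article*

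**What the plan says.** Section 2.9 (Secondary outcomes) sets out the metagenomic analysis in one sentence with two parts. Diversity comes first: "analysing alpha diversity and beta diversity in each group to determine the intra-groups differences in the microbiota compositions". Taxonomy follows: "analysing the inter- and intra-groups taxonomic characteristics at the levels of phylum, genus, and species". The next sentence adds a functional analysis: "Metagenomic biological pathway analysis are used to evaluate the effect of probiotics on the function of the gut metagenomics".

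Section 2.15 (Statistical analysis) has a short paragraph on metagenomics and metabolomics. It names the t-test, Wilcoxon and Kruskal-Wallis procedures and says that the "test will be used to evaluate differences in various variables between and within groups". The adonis P-value "will be generated based on 999 permutations", and P "values will be corrected for multiple testing using the Benjamini-Hochberg procedure". The paragraph does not mention diversity and does not give the grouping factor for adonis. The between-group Z test earlier in 2.15, with its Table 2, covers five clinical scores and no microbiome measure.

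The abstract lists the gut microbiome among the secondary outcomes and says that each outcome is assessed over time "to identity inter- and intra-groups differences".

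The microbiome result also has a consequence. The note to Table 1 says that the faecal metabolome will be measured "when data analysis finds that the probiotics present significant effect on gut microbiome". Section 2.14 states the converse: with no effect on the microbiome, the metabolome is not assayed.

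**The concern.** The sentence in 2.9 uses the within-group term for diversity and both terms for taxonomy, side by side. Read as written, diversity is examined for change over time inside each arm. Such a change is not an effect of randomised treatment, because anything that moves both arms produces it too. The protocol supplies candidates: both arms take a daily powder containing maltodextrin, orange powder and maltitol (2.6), both must stop other probiotics and foods such as yoghurt (2.7), and antibiotic use and dietary change may occur and are recorded (2.6, 2.11).

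Two uses of the result are at stake. One is the decision to run the metabolome assays, which depends on a probiotic effect that the text does not define. The other is the Discussion's argument that the omics data form the first link in a chain running to symptoms and mood. Within-arm diversity changes cannot carry that link.

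**Working it through.** The protocol gives no figure for this point, so the check is mainly a comparison of the texts.

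**Which comparison is stated for which microbiome measure**

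| Place | Measure | Comparison stated |
|---|---|---|
| Abstract, Method | every outcome, microbiome included | between and within groups |
| 2.9 | alpha and beta diversity | within each group |
| 2.9 | taxonomy (phylum, genus, species) | between and within groups |
| 2.9 | pathways | effect of the probiotic; comparison not stated |
| 2.15, omics paragraph | unnamed variables | between and within groups |
| 2.15, omics paragraph | adonis | grouping factor not stated |
| Table 1 note; 2.14 | microbiome effect as metabolome gate | measure and comparison not stated |

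The only text that names diversity gives it the within-group comparison. The texts that would give it a between-group comparison are general and do not name it. Nothing says which prevails.

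**Illustration of why within-arm tests are not enough**

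Inputs: 100 volunteers per group (2.13), or 100 × (1 − 0.20) = 80 after the 20% drop-out allowed there. Assumptions that are not in the protocol: a paired within-arm test at two-sided 0.05 by normal approximation; independent arms; and the same true change d, in standard deviations of the change, in both arms, so that there is no probiotic effect.

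Chance that one arm is significant: p = 1 − Φ(1.96 − d√n) + Φ(−1.96 − d√n).

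Chance of significance under probiotic and not under placebo: p(1 − p).

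| d | p, n = 100 | p(1 − p), n = 100 | p, n = 80 | p(1 − p), n = 80 |
|---|---|---|---|---|
| 0 | 0.050 | 0.048 | 0.050 | 0.048 |
| 0.1 | 0.170 | 0.141 | 0.145 | 0.124 |
| 0.2 | 0.516 | 0.250 | 0.432 | 0.245 |
| 0.3 | 0.851 | 0.127 | 0.765 | 0.180 |
| 0.4 | 0.979 | 0.020 | 0.947 | 0.050 |

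Example: with n = 100 and d = 0.2, d√n = 2, so p = 1 − Φ(−0.04) + Φ(−3.96) = 0.516 and p(1 − p) = 0.516 × 0.484 = 0.250.

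The product p(1 − p) cannot exceed 0.5 × 0.5 = 0.25. With no change in either arm it is 0.05 × 0.95 = 0.0475. It rises to the maximum at 50% within-arm power and falls again as both arms become almost certain to be significant (0.8 × 0.2 = 0.16 at 80% power). If a significant change in the probiotic arm alone were taken as the effect, the column p applies, and it keeps rising with d.

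**The case against.** The strongest reply is that between-arm analysis is already planned. The abstract's aim covers each outcome measure. The omics paragraph in 2.15, which is the statistics section, plans tests between and within groups, and adonis may well compare arms. The Discussion repeats that both kinds of difference will be analysed. The wording in 2.9 may also be a slip: in 2.15 the within-group Kruskal-Wallis analysis is followed by a pointer to Table 3 for inter-group differences, whereas Table 3 is titled as within-group.

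Much of this stands. A reader might infer from 2.9 that the trial will compare diversity within groups only and so cannot show a probiotic effect on it. The article as a whole does not support that, because the abstract and 2.15 leave room for a between-arm comparison. The Discussion helps less, since its statement is tied to defecation and quality of life and the microbiome is brought in afterwards. A possible slip does not remove the conflict either; it is a reason to correct the sentence.

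A reader might also infer that a within-arm diversity change would trigger the metabolome assays. The documents do not say so. The gate refers to the gut microbiome, not to diversity, and between-arm taxonomy could decide it. No passage adopts significance in one arm and not in the other as a rule. What stands is that the gate names no measure or comparison, so that reading is open.

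Finally, the percentages are not properties of this plan. They depend on an equal change in both arms and on a decision rule that the protocol does not state.

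**Conclusion.** The point holds as a conflict between a specific statement and general ones. Section 2.9 gives diversity a within-group comparison that cannot isolate a randomised effect; the abstract and 2.15 point to between-group analysis without naming diversity; and the metabolome gate leaves the deciding comparison open.

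Size: minor. The outcome is secondary and mechanistic, and the primary analysis is unaffected. A gate wrongly passed would cost assays and weaken the mechanistic argument, not the efficacy conclusion. The range from about 5% with no change in either arm to a ceiling of 25% is an illustration. It rests on equal change in both arms, independent arms, two-sided tests at 0.05 and a reading of the gate that the text permits but does not state; at very high within-arm power the figure drops below 5%.

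**What to change.** State in 2.9 and 2.15 that alpha diversity at day 28 (and day 42) is compared between arms with adjustment for day 0, and that beta diversity is compared between arms by adonis with one sample per volunteer in each test. Keep within-arm changes as descriptive results. In the Table 1 note and in 2.14, base the metabolome decision on a named between-arm microbiome result.

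The cost is a few sentences and a few lines of code. Stool samples at days 0, 28 and 42 are already planned, so no new data are needed. If the full protocol or analysis plan already contains these comparisons, aligning the wording is sufficient.

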
### Safety evaluation

2.10

Existed evidence shows that probiotics is safe, without significant adverse event (AE) compared with placebo group. Nevertheless, in the present study, four kinds of symptoms possibly related to probiotics are listed as possible AEs in the study, including symptoms may result from systemic infections, deleterious metabolic activities, excessive immune stimulation, and gastrointestinal side effects [39]. And severe AEs are those AEs result in volunteer's withdrawal, like hospitalization, disability, mortal danger, or death. When an AE occurs, the symptoms, time of onset, duration, causal relationship with interventions, and measures taken, will be accurately recorded during the study. Any serious AE will be recorded according to the corresponding criteria and emergency measures and promptly reported to the medical ethics committee of the first affiliated hospital of Nanchang university within 24 h, in addition, a separate AE report will be prepared. Judged from the AEs observed in the study, the safety of *L. plantarum* P9 powder will be evaluated as the following four levels: excellent (safe with no AE); good (relatively safe with moderate AEs that disappear on their own without any specific treatment); conditional (AEs that resolve after adopting certain measures and do not lead to study withdrawal); and unsafe (AEs that result in volunteer's withdrawal) [40].

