### Additional assessment

2.11

Demographic profiles, special situations related to defecation during the study, including change of dietary habits (e.g., eating spicy or oily foods or drinking), taking antibiotics and any other reported situation are recorded and assessed as needed.

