### Data collection and monitoring

2.14

An independent data management team (DMT) is formed to periodically assess the study quality and safety. Volunteers are required to complete the defecation diary (Appendix 2) daily online and the DASS-21 (Appendix 3) online as scheduled in Table 1, both of which are promptly downloaded and collected by the data analysts. The data of demographic profiles, defecation diary (Appendix 2) and DASS-21 (Appendix 3) completed online by volunteers can downloaded as excel spreadsheets for further analysis. For gut microbiome and metabolomics test, volunteers have to prepare stool samples as the instructions of test kit at home, at day 0 (observing period of pre-administrating), 28 (observing period of administrating) and 42 (observing period of pro-administrating), all of which are timely collected, separately stored and sent for detection at −80 °C in a special stool storage kit from Guangdong longsee company (www.longseemed.com). The data of gut microbiome and metabolomics detected from stool samples will detected by Key Laboratory of Dairy Biotechnology and Engineering, Ministry of Education.

All the data will be submitted to the DMT for managing and monitoring. The DMT will promptly check the data and urge the data collectors to resolve it when uncertainty about the data occurs. All records that contain names, ID Number, or other personal identifiers (e.g., informed consent forms), are stored separately from study records. The database will be password protected by the DMT. The team also has the authority to carry out an interim analysis or terminate the next-step study according to the following situations [1]: if the probiotics does not present effect on gut microbiome, then the study will not further conduct the detections of faecal metabolome [3]; if any severe adverse events related to probiotics occurs, DMT will suggest terminating the study.

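### Adverse events are framed by four suspected probiotic-type symptoms and scheduled for assessment only at days 14, 28 and 42, so other harms may go uncounted

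*Protocol article*

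**What the plan says.** Section 2.10 (Safety evaluation) states that "four kinds of symptoms possibly related to probiotics are listed as possible AEs in the study", and names them as "symptoms may result from systemic infections, deleterious metabolic activities, excessive immune stimulation, and gastrointestinal side effects". Section 2.12 (Compliance monitoring and withdrawn) points back to the same four categories as grounds for withdrawal. For each event, "When an AE occurs, the symptoms, time of onset, duration, causal relationship with interventions, and measures taken, will be accurately recorded during the study". A serious event is to be "promptly reported to the medical ethics committee of the first affiliated hospital of Nanchang university within 24 h". Section 2.10 then gives the product one of four safety levels according to the AEs seen. The best level requires no AE, and the worst is for AEs that lead to withdrawal.

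Table 1 (section 2.6) ticks the AE and SAE rows at Visits 2, 3 and 4 (days 14, 28 and 42). On daily contact, section 2.14 says: "Volunteers are required to complete the defecation diary (Appendix 2) daily online". Section 2.11 (Additional assessment) lists, among special situations related to defecation, that "taking antibiotics and any other reported situation are recorded and assessed as needed".

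**The concern.** A placebo-controlled safety comparison is useful largely because it can show harms nobody expected. A frame built from symptoms already thought to be linked to the product works against that. It lets suspected cause influence which events are recorded, although cause should be judged after recording. An event that staff or volunteers do not recognise as one of the four kinds may never be written down as an AE.

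Two features add to this. Every volunteer has a chronic bowel disorder and gastrointestinal side effects are one of the four kinds, so some gut complaints will pre-date dosing. Volunteers also take the product at home, and the scheduled look for harm comes only every two weeks.

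What is at stake is the safety grade. It is read directly from the AEs observed, so under-ascertainment would make the product look safer than the data warrant.

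**Working it through.** The plan states no figure on this point that could be reproduced. Apart from visit spacing and enrolment counts, the check sets the passages side by side.

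**1. What counts as an AE.** Section 2.10 offers only the four-kind list. Section 2.12 treats that list as the trial's AE categories. The Abstract says without restriction that adverse events will be recorded, but it defines nothing. The article therefore contains one operative description, and it is built on suspected relation to probiotics.

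**2. What depends on it.** The four-level grade in section 2.10 depends on which events are counted. So does the data management team's power in section 2.14 to suggest termination after a severe event related to the product. Both need an event to be recognised and recorded first.

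**3. When harm is looked for.** Table 1 gives days 14, 28 and 42, with day 0 as the start of dosing. The gaps are 14 − 0 = 14, 28 − 14 = 14 and 42 − 28 = 14 days. Fourteen days is the interval between scheduled assessments. It would be the longest detection delay only if events were found at visits and nowhere else, which the article does not say.

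**4. By what route events arrive between visits.** Section 2.1 has volunteers dosing at home and followed online. The diary content described in sections 2.7 and 2.8 is defecation frequency, stool appearance, urgency, and substances or drugs related to defecation. Section 2.10 says what is recorded once an event occurs and how soon a serious one is reported. It does not say how the team learns of the event, or when the 24 h begin.

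**5. What baseline exists.** Stool frequency, consistency and urgency have one: the diary for days −14 to −1 and the day-0 severity score (Table 1 note; section 2.8). No baseline record is described for other gut symptoms such as pain or bloating. Onset time is recorded for each AE, but at a visit two weeks later it may rest on recall.

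**6. Antibiotics.** Systemic infection is one of the four kinds. Section 2.6 anticipates antibiotic use during administration, and section 2.11 records it as a defecation-related situation. Neither section links it to an AE assessment.

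**7. Room left to change.** Section 4 (Trial status) reports 174 enrolled of a planned 200. That is 174/200 = 87%, leaving 200 − 174 = 26 volunteers for whom a new baseline item could be collected prospectively.

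**The case against.** The best defence is that the article does not state any of the feared consequences, and a reader might infer three that go too far.

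- **Unlisted events are excluded by rule.** They are not. The list is of possible AEs and is not declared exclusive, and the Abstract's statement is unrestricted. The severe-event definition names hospitalization and death with no limit on cause, so an unrelated hospital admission is not shut out of the 24 h report. Causality is also recorded for each AE, so it is not settled by the definition.
- **Pre-existing gut symptoms are counted as new AEs.** No section says so. Onset and duration are recorded, and the main stool symptoms have a baseline. A blank day-0 AE cell is ordinary, because dosing starts then. Any figure for how far pre-existing symptoms would dilute an arm difference would need assumed symptom rates and would have to ignore the recorded onset time.
- **A serious event surfaces up to 14 days late.** This requires detection at visits only. The plan records an AE when it occurs and sets a 24 h report. Between visits it also has a daily diary, a WeChat group and a team that checks data promptly.

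Section 2.7 also asks for an explanation of defecation-related drugs in the diary, so part of the information on antibiotics may already be captured. Finally, a condensed article may leave a general AE definition, a checklist and a reporting route to the full protocol.

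All of this limits the point to a risk. It does not remove it. The article does more than stay silent: it states a frame based on suspected cause, repeats it in section 2.12, and grades safety on the result. The contact channels exist, but none is described as asking about general health.

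**Conclusion.** The point holds as a risk of under-ascertainment. Harms outside the four kinds may go uncounted, non-stool gut symptoms present before dosing may be hard to separate from new ones, and events that nobody volunteers may reach the team late. The documents give no AE rates and do not restrict detection to visits, so no numerical bias or delay can be put on it.

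The conclusion assumes that the four-kind list guides what staff record, as section 2.12 suggests. It also assumes that the diary form in Appendix 2, which is not shown, asks no more than the text describes. If the form already has an open health question, or the full protocol already defines AEs regardless of cause, the matter reduces to bringing the article's wording into line. Otherwise the change should be made: it is cheap, and the safety grade depends on it.

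**What to change.** 1. **Section 2.10:** define an AE as any untoward medical event after consent, whatever its kind or suspected cause. Keep the four kinds as prompted events of special interest.
2. **Table 1:** add a day-0 checklist of gut symptoms that the diary does not cover. Repeat it at the AE visits, and count only symptoms that are new or worse than at day 0.
3. **Daily diary (Appendix 2):** add one open item on new illness, hospital visit or antibiotic use, with a positive answer opening an AE record. State in 2.10 when the 24 h reporting period begins.
4. **Volunteers already enrolled:** a day-0 checklist cannot be recovered for those already dosed. Before safety is graded, have the recorded special situations of all volunteers reviewed, blinded to group, against the broad definition. Report which events were found this way.

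The cost is a changed definition, a short checklist, one diary item and one blinded review. The downside is more AE records to process and a slightly longer daily diary. Because 87% were enrolled when the article was written, the prospective items help only the remainder, and most of the benefit comes from step 4.

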### Compliance monitoring and withdrawn

2.12

The L. *plantarum* P9 and placebo powder are supplied as treatment packs and packaged in boxes. At the beginning of administration phase, the probiotics or placebo packaging boxes enough for 28-day intervention are distributed to corresponding volunteers. Volunteers are required to keep all the used (empty) and unused treatment packs which are collected to check whether a volunteer takes the probiotics or placebo as the study's schedule. Based on the number of empty packs, the compliance rate is calculated for individual volunteer. A compliance rate ≥80% indicates a good compliance. To improve compliance, a WeChat group is established for the cohort of volunteers, and the study personnel can post messages via the WeChat group, reminding volunteers to take the samples as scheduled and complete the defecation diary (Appendix 2). In addition, each volunteer can receive 300 RMB as a reward once they complete the follow-up.

Volunteers can withdraw from the trial for the following reasons [1]: Persistent adverse reactions (cannot be resolved after taking certain measures) possibly involving the four kinds of AEs listed in “Safety evaluation part” [2,39] Volunteers can autonomously withdraw from the study at any time for any reason.

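### The product safety grade is absolute: it uses no event rate, placebo comparison or recorded causality, and the terms severe and serious are left unreconciled

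*Protocol article*

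**What the plan says.** Section 2.10 (Safety evaluation) makes the powder the thing graded, on the AEs seen in the study. It "powder will be evaluated as the following four levels: excellent (safe with no AE"). The second level covers moderate events that clear without specific treatment. The third is "conditional (AEs that resolve after adopting certain measures and do not lead to study withdrawal") and the last is "unsafe (AEs that result in volunteer's withdrawal"). The same section lists gastrointestinal side effects among its four AE classes and has the causal relationship recorded for each AE, but no level uses it.

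The terms for the gravest events vary:

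- Section 2.10 defines one class by withdrawal: "severe AEs are those AEs result in volunteer's withdrawal, like hospitalization, disability, mortal danger, or death".
- Section 2.10 then switches term for expedited reporting: "Any serious AE will be recorded according to the corresponding criteria and emergency measures and promptly reported to the medical ethics committee", within 24 hours. The criteria are not printed.
- Table 1 has its own row for serious adverse events at days 14, 28 and 42.
- Section 2.14 (Data collection and monitoring) returns to the other term: "if any severe adverse events related to probiotics occurs, DMT will suggest terminating the study".

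Section 2.15 (Statistical analysis) names five clinical outcomes for between-group testing, and AEs are not among them. Its main dataset is the volunteers who completed follow-up.

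**The concern.** A placebo arm shows how many events would have occurred without the active product. The printed grade ignores that information. In volunteers enrolled for long-standing loose stools, some gastrointestinal complaints and some withdrawals because of them can be expected on either powder. A grade triggered by such events measures the number of volunteers observed and the background rate as much as any effect of the probiotic. It can condemn an inert product, and it hardly changes when the true risk doubles. Safety is a stated aim of the trial, so this grade is likely to be reported as its safety conclusion.

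The terminology raises a second, smaller problem. The class tied to withdrawal, the class tied to 24-hour reporting and the class tied to termination advice carry two names with no stated relation. It is therefore unclear which events belong to which.

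**Working it through.** **Inputs.** Section 2.10 states no figure. The only number needed from the article is the arm size, 100 per group (section 2.13). Its starting value reproduces: with a difference of 3, SD 6.8, two-sided α = 0.05 and 80% power, n = 2 × [6.8 × (1.960 + 0.842)/3]² = 80.65, so 81 as stated. Then 81 × 1.2 = 97.2, matching the stated 97, which the article rounds up to 100.

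**Assumptions.** The article gives neither an AE rate nor an AE-withdrawal rate, so the rate p is assumed and shown over a range. The article also does not say how events combine into one grade. The calculation takes a single AE withdrawal in the probiotic arm as enough for *unsafe*, and any AE as enough to lose *excellent*.

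**Chance that an inert powder is graded *unsafe*:** 1 − (1 − p)^100.

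| Assumed background AE-withdrawal rate | Chance of *unsafe* |
|---|---|
| 0.1% | 10% |
| 0.5% | 39% |
| 0.69% | 50% |
| 1% | 63% |
| 2% | 87% |
| 5% | 99% |

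The 50% point is 1 − 0.5^(1/100) = 0.69%. Section 2.13 allows up to 20% drop-out, and 0.69/20 is about 3.5%. So at a full 20% drop-out, one half is reached if about 3.5% of drop-outs are due to AEs. With 80 volunteers the 50% point is 0.86%. If events from both arms are pooled (200 volunteers), it is 0.35%.

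**Chance of *excellent*:** (1 − p)^100, with p now the rate of any AE. At 1% it is 37%, at 5% it is 0.6%.

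**Discrimination.** If the true AE-withdrawal rate doubles from 2% to 4%, the chance of *unsafe* moves only from 87% to 1 − 0.96^100 = 98%.

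**Comparing arms instead.** Take 100 per arm, equal true rates, and a two-sided Fisher exact test at 0.05 that flags only when the probiotic arm is worse. An inert powder is then flagged with probability 0.0002, 0.002 and 0.010 at rates of 1%, 2% and 5%. These values are low partly because the exact test is conservative with few events. A non-significant result would not show safety, so an interval is more useful than a test.

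**Terms side by side.** Take a volunteer who is hospitalised, recovers after treatment and stays in the trial. On a literal reading of the withdrawal-based definition in section 2.10, the event is not *severe* and is graded no worse than the third level. Whether it counts as *serious* depends on the unprinted criteria. Whether it reaches the section 2.14 trigger, if related to the probiotic, depends on what *severe* means there. An event that neither resolves nor leads to withdrawal fits none of the four levels.

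**The case against.** The strongest reply has four parts.

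- **Aggregation is not stated.** The level descriptions read like courses of single events, and nothing says that one event fixes the product's grade. This stands in part. The sentence does name the powder as what is graded, but the one-event rule is an assumption, and every probability of *unsafe* above depends on it.
- **The rates are assumed.** This also stands. A reader might infer that an inert product would probably be called *unsafe*. The article does not support that without conditions: it gives no rate, and below about 0.69% the chance is under one half. The calculation also counts background events whatever their judged cause, whereas section 2.10 frames AEs as symptoms possibly related to probiotics. The general right to leave, "Volunteers can autonomously withdraw from the study at any time for any reason", adds nothing, because withdrawals for other reasons do not trigger the grade. The adverse-reaction reason beside it in section 2.12 is limited to persistent reactions.
- **An AE table by arm may be in an unseen analysis plan.** Fair, and its absence from the article is not the point. The printed grading rule would still not use such a table.
- **Serious events are handled separately.** A reader might infer that a hospitalised volunteer who stays in is missed, or escapes the 24-hour report. The article does not support this. Every AE is recorded, the 24-hour report attaches to *serious* and not to the withdrawal-based term, and the serious-event row in Table 1 carries no withdrawal condition. The definition in section 2.10 can also be read as naming hospitalisation as severe in itself. Only the unexplained mix of terms remains.

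**Conclusion.** The point holds in this form. The grade in section 2.10 is absolute and uses no rate, placebo comparison or recorded causality, so it cannot separate harm from background. This follows from the printed text and needs no assumed rate.

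Its size is conditional. If one AE withdrawal suffices and 100 volunteers take the powder, an inert product is graded *unsafe* with probability 10% to 39% at background rates of 0.1% to 0.5%, and 63% to 99% at 1% to 5%.

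On terminology, a hospitalised volunteer who does not withdraw may, on a literal reading, fall outside the *severe* and *unsafe* classes. The event would still be recorded, and a serious-event reporting route exists. The primary efficacy analysis is not affected. The change should be made because safety is one of the trial's stated conclusions.

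**What to change.** Base the safety conclusion on a comparison of arms among all randomised volunteers who took study powder. Report by arm the number and percentage with any AE, any serious AE and any AE leading to withdrawal, each with a risk difference and 95% confidence interval. State the population explicitly, because the completers' dataset in section 2.15 would leave out volunteers who withdrew because of an AE. Use the four levels only to describe individual events.

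Separately, reconcile the withdrawal-based *severe* class and the *serious* class in section 2.10, the serious-event row in Table 1 and the termination advice in section 2.14, so that the relation between the terms is stated. What the reporting or termination rule should be is for the sponsor and investigators to decide.

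The cost is some wording and one table. The AE details are already being collected, so no new data are needed.
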